#### Active intervention: real 4-step method

Participants will come to the laboratory at 7:00 a.m. and we will first obtain a resting, fasted venous blood sample (via venipuncture) for the laboratory evaluations previously listed. The iPro2 Professional continuous glucose monitor (CGM) with Enlite sensor (Medtronic, MN, USA) will be installed at that time. Participants will then consume a standardized cereal-based breakfast meal (sugar-coated corn flakes, peaches, and semi-skimmed milk; 1.3 g carbohydrate · kg^-1^ body mass). At 1:00 p.m. participants will consume a standardized pasta-based lunch meal (pasta, tomato-based sauce, cheddar cheese, olive oil; 1.3 g carbohydrate · kg^-1^ body mass). Between the morning and evening visits, participants will record their self-measured glucose control every 2 h.

At 5:00 p.m. participants will arrive for the evening training session. Before starting this session, they will self-administer a 50% reduced pre-meal rapid-acting insulin dose into the abdomen (the injection site will be at the mid-point between the iliac crest and the navel). Immediately after receiving this insulin dose, participants will consume a pre-exercise carbohydrate bolus (sugar-coated corn flakes, peaches and semi-skimmed milk; 1.0 g carbohydrate · kg^-1^ body mass). Following this bolus, participants will remain rested for 60 min, at which point a finger stick sample for glucose testing will be drawn immediately before starting with the training sessions.

At 60 min post-exercise, participants will self-administer a pre-meal rapid-acting insulin dose reduced by 50%, into the abdominal site contralateral to the previously administered pre-exercise rapid-acting insulin injection. After receiving this insulin dose, participants will consume a carbohydrate-based meal (basmati rice, tomato-based sauce, turkey breast, and an isomaltulose orange flavored drink (10% solution); 1.0 g carbohydrate · kg^-1^ body mass) designed to elicit a low GI (GI = 37) response [2].

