Following this meal the participants will be discharged and will continue recording interstitial glucose values with the CGM until the subsequent morning visits. At 180 min following the post-exercise meal (240 min post-exercise), participants will consume a low-GI bedtime snack (low fat yogurt with honey tap; GI = 38), equivalent to 0.4 g carbohydrate · kg^-1^ body mass, and will omit rapid-acting insulin. In order to improve adherence, participants will be contacted before the bedtime snack to ensure compliance, and they will be encouraged to replicate their sleeping patterns as much as possible prior to the training sessions.

The basal insulin dose after exercise will be reduced by 20% of the pre-trial basal dose. Nevertheless, the timing will be maintained throughout as per each participant’s individual regimen. Twenty-four hours afterwards, participants will return to their usual full basal insulin dose.

At 8:00 a.m. on the morning following each training assessment, participants will return to the laboratory. Here we will obtain another fasting blood sample through venipuncture and subsequently provide them with a standardized breakfast meal (sugar-coated corn flakes, peaches, semi skimmed milk; 1.0 g carbohydrate · kg^-1^ body mass). With this meal, they will self-administer their full unchanged rapid-acting insulin dose.

Following the consumption of breakfast, the participants will be discharged from the laboratory and instructed to maintain CGM for an additional 11 h (i.e., 24 h from exercise cessation). Also during this time, they will continue to monitor their diet using a food record diary and weighing their foods. We will provide the participants with a smartphone application for the recording of this information (MyFitnessPal App).

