#### Control intervention: usual recommendations (sham 4-step method)

Recently, ADA published a position statement about physical activity and diabetes [16]. This statement explained how the variable glycemic responses observed in association with physical activity makes it very difficult to provide uniform recommendations for both the management of food intake and the insulin dosing regimen. Nonetheless, several instructions in this document are intended to help prevent hypoglycemia. To prevent low blood glucose level during prolonged (>30 min), predominantly aerobic exercise, additional carbohydrate intake and/or reductions in the insulin dose are typically required [12–16]. In addition to the changes in insulin regimen and carbohydrate intake, a brief (10 s) maximal intensity sprint could be performed before or after the exercise session, as suggested in the ADA guidelines, to prevent exercise-induced hypoglycemia [12]. The position statement also recommends adjusting daily basal insulin dose with reduced prandial bolus insulin and low-GI carbohydrate feeding following evening exercise for those on multiple daily injections [12]. Finally, inclusion of a bedtime snack, overnight glucose checks, or alarms and automatic pump suspension may also be warranted [16].

Patients allocated to the control group, or sham 4-step Method, will receive current usual recommendations as stated by the ADA [16], but following the scheme established with the real 4-step method (see Table 2 for the comparison for both interventions). Prior to exercise, the CGM will be installed at 7:00 a.m., and they will receive their meals in the same amount and frequency as in the real 4-step method, consisting of a breakfast at 8:00 a.m., lunch at 1:00 p.m. and pre-exercise meal at 5:00 p.m. All of the three meals will have the same caloric content as in the real intervention, and there will be no insulin modification for the first two meals. Assuming that they will be performing moderately intense physical activity later in the day, for up to 60 minutes, this group will receive a rapid-acting insulin dose that will be 75% of their usual dose concomitantly with the 5:00 p.m. meal prior to the onset of physical activity.

**Table 2 Tab2:** Scheme comparison of interventions delivered in the real and sham 4-step methods

Time		Real 4-step method	Control (sham) 4-step method
8:00 a.m.	Breakfast	Standardized cereal-based breakfast	Standardized cereal-based breakfast

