	Insulin dose	Unchanged	Unchanged
1:00 p.m.	Lunch	Standardized pasta-based lunch	Standardized pasta-based lunch
	Insulin dose	Unchanged	Unchanged
5:00 p.m.	Pre-exercise meal	1 g · kg^-1^ CHO bolus	1 g · kg^-1^ CHO bolus
	Insulin dose	50% reduction	75% reduction
7:00 p.m.	Post-exercise meal	Low-GI 1 g · kg^-1^ CHO bolus	Medium-GI 1 g · kg^-1^ dinner
	Insulin dose	50% reduction	No reduction
10:00 p.m.	Snack	Low-GI 0.4 g · kg^-1^ CHO snack	Medium-GI 0.4 g · kg^-1^ CHO snack
	Insulin dose	No insulin administered	No insulin administered
Regular hour for basal insulin	Insulin dose	20% reduction	No reduction

*CHO* carbohydrates, *GI* glycemic index

One hour after finishing the exercise session, the participants will receive a carbohydrate-based meal with the same caloric content as the meal apportioned in the real interventional arm; however, we will not use low-GI food for this bolus. Contrarily we will give the participants traditional rice, tomato sauce, turkey breast, and water. With this meal we would be providing about 1.0 g of carbohydrate · kg^-1^ of body mass. We will not modify the insulin dosage administered with this meal, considering that the ADA guidelines do not suggest any specific change around this issue.

Participants will then go home where they will continue registering interstitial CGM. About 180 min after dinner (approximately 240 min after finishing the exercise session), the participants will be contacted to remind them to eat a snack before going to bed. However, this will differ from the real intervention in that this will not be a low-GI snack (200 mL of unsweetened orange juice and half a banana), and will be equivalent to 0.4 g of carbohydrate · kg^-1^ of body mass. Additionally, participants will not administer any insulin dose with this snack.

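### Table 2 sets the post-exercise insulin, meal and snack too early by the length of the exercise session (about 60 min); with the stated rest and wait, no time is left for exercise

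*Protocol article*

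**What the plan says.** Both arms take the pre-exercise rapid-acting insulin and meal at 5:00 p.m. The section on the real 4-step method says "At 5:00 p.m. participants will arrive for the evening training session", that dose and meal follow, and then "participants will remain rested for 60 min, at which point a finger stick sample for glucose testing will be drawn immediately before starting". The control section gives its dose "concomitantly with the 5:00 p.m. meal prior to the onset of physical activity". It states no rest period of its own, but has controls treated by "following the scheme established with the real 4-step method (see Table 2 for the comparison for both interventions").

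After exercise the two arms use the same intervals. Real arm: "At 60 min post-exercise, participants will self-administer a pre-meal rapid-acting insulin dose reduced by 50" per cent, with the meal straight after and the snack 180 min after that meal, which the text equates with 240 min after exercise. Control arm: "One hour after finishing the exercise session, the participants will receive a carbohydrate-based meal", and "About 180 min after dinner (approximately 240 min after finishing the exercise session), the participants will be contacted" about the snack.

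Table 2 turns this into clock times shared by both arms: pre-exercise meal and insulin at 5:00 p.m., post-exercise meal and insulin at 7:00 p.m., snack at 10:00 p.m.

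Three other statements bear on the clock. The LIST-P section plans all evaluations to take about 60 min. The real-arm section has participants keep the CGM on for 11 h after the next morning's breakfast (visit at 8:00 a.m.) and equates this with 24 h after exercise ended. The Outcomes section says the soccer evaluation is performed at 5:00 p.m.

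**The concern.** The 5:00 p.m. and 7:00 p.m. rows of Table 2 are two hours apart. The prose needs one hour of rest before exercise and one hour of waiting after it, so the table has no room for the session itself. The snack row fails in the same way.

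Table 2 is the only side-by-side insulin and meal schedule, and the control section sends the reader to it. Staff who worked from its clock times would give rapid-acting insulin at about the end of a 6:00 to 7:00 p.m. session instead of 60 min later, at half dose in the real arm and full dose in controls. The snack would come about 180 min after exercise instead of 240. Staff who kept the clock times by shortening the rest or the wait would also depart from the text. These intervals are part of the intervention, and the primary outcome is hypoglycemia in the 24 h after the session.

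**Working it through.** Inputs:
- Pre-exercise dose and meal: 5:00 p.m. (both arm sections and Table 2).
- Rest before exercise: 60 min (real-arm section; for controls inferred from the shared scheme).
- End of exercise to dose and meal: 60 min (both arm sections).
- End of exercise to snack: 240 min (both arm sections).
- Session length S: about 60 min (LIST-P section).
- Table 2: 7:00 p.m. and 10:00 p.m.

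**1. What Table 2 gets right.** Meal to snack: 10:00 − 7:00 = 180 min. The prose gives 240 − 60 = 180 min. The gap agrees, so any fault is one common shift of both rows.

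**2. Time left for exercise.** Between the insulin rows: 7:00 − 5:00 p.m. = 120 min, and 120 − 60 (rest) − 60 (wait) = 0 min. From the snack row: 10:00 p.m. − 240 min = 6:00 p.m., which is also the earliest start (5:00 p.m. + 60 min), so again 0 min. No session longer than zero fits.

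**3. Size of the shift.**
- Dose and meal = 5:00 p.m. + 60 + S + 60 = 7:00 p.m. + S.
- Snack = 5:00 p.m. + 60 + S + 240 = 10:00 p.m. + S.

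Both rows are early by exactly S.

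| S | Basis | Dose and meal | Snack |
|---|---|---|---|
| 53 min | LIST-P only: 3 × 15 + 2 × 4 | 7:53 p.m. | 10:53 p.m. |
| 60 min | planned session length | 8:00 p.m. | 11:00 p.m. |
| about 80 min | listed components summed | 8:20 p.m. | 11:20 p.m. |

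The 80 min is 53 (LIST-P with rests) + 5 (recovery) + 2 × 10.4 (LSST) + 2 × 0.7 (LSPT) ≈ 80.3. Each LSST is ten shots at the 8.5 s limit with nine 1-min rests: (85 + 540)/60 = 10.4 min. Each LSPT is taken at its 43 s allowance. The sum allows no changeover time and is illustrative only.

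**4. Cross-check from the CGM sentence.** 8:00 a.m. + 11 h = 7:00 p.m., said to be 24 h after exercise ended. Exercise therefore ends at about 7:00 p.m., the minute at which Table 2 serves a meal due one hour later.

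**5. Whether a 5:00 p.m. start rescues the table.** Under Outcomes read literally, exercise runs 5:00 to 6:00 p.m., the meal is at 7:00 and the snack at 10:00 p.m., as in Table 2. But the pre-exercise meal would then have to be at 5:00 p.m. − 60 min = 4:00 p.m., against both arm sections and Table 2 itself. The CGM interval from 8:00 a.m. would be 10 h, not 11 h. This reading repairs two rows by breaking a third.

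**The case against.** **The rest period is explicit in one arm only.** This is correct. For controls the text says only that the 5:00 p.m. dose precedes activity; the 60 min comes from the instruction to follow the real arm's scheme. The inference is strong but remains an inference, and the zero-minute result for controls depends on it.

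**The CGM check is approximate.** The 11 h run from after breakfast, not from 8:00 a.m. sharp, and Outcomes keeps the CGM on until 48 h after the session. The first point stands, but any delay moves the implied end of exercise later, further from Table 2. The second concerns how long the device is worn, not when exercise ended. The sentence corroborates; the contradiction does not need it.

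**Replacement clock times are insecure.** This also stands. 8:00 and 11:00 p.m. hold for a 60-min session, and the listed components could take longer. Only intervals counted from the end of exercise are safe.

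**The practical risk is small.** Largely accepted. The row is labelled as post-exercise, the prose in both arms ties the dose to the end of exercise, and the meal is given on site ("Following this meal the participants will be discharged"). The snack is prompted by contact. With exercise from 6:00 p.m., 7:00 p.m. arrives at about the end of the session or during it, so the slip would probably be noticed. The primary outcome window is counted from the session, not from Table 2.

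**Conclusion.** The contradiction is certain for the real arm and follows for controls once the shared scheme is taken to include the rest. Table 2's 7:00 p.m. and 10:00 p.m. rows are early by the session length: about 60 min on the protocol's own planning figure, at least 53 min from LIST-P alone, and more if the session runs over. The balance of the text (the 5:00 p.m. meal, the rest, the two post-exercise intervals and the CGM sentence) points to the table rows and the 5:00 p.m. start under Outcomes as the statements to correct. It should be fixed because this is an insulin schedule in a hypoglycemia trial, though the risk is limited.

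Two stronger readings are not supported. A reader might infer bias between the arms, but the clock times are the same in both, so none is claimed. A reader might also infer that the post-exercise insulin will be mistimed in practice. That happens only if staff follow the table's clock over the prose, and nothing in the document says they would.

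**What to change.** - In Table 2, replace 7:00 p.m. with 60 min after the end of exercise, and 10:00 p.m. with 240 min after the end of exercise. If clock times are wanted as a guide, give roughly 8:00 and 11:00 p.m. for a 60-min session, later if it runs longer.
- Have staff note the end-of-exercise time at each session. The protocol does not say that this is recorded, and both intervals depend on it.
- State the 60-min rest explicitly for both arms.
- Under Outcomes, give arrival at 5:00 p.m. with exercise from about 6:00 p.m.

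The cost is a text correction to two table rows and two sentences, plus one time entry per session. No dose or interval changes. The article lists recruitment as pending, so the correction could precede the first session.

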### Trial design

This is a randomized, crossover, double-blinded (subject and evaluator), controlled trial. Participants will be randomized to the order of the interventions assigned (real 4-step method versus usual recommendations (sham 4-step method)), leaving a washout period of 3 weeks for repeating assessments after switching groups. We follow the standard protocol items: recommendation for interventional trials (SPIRIT) guidelines to cover all sections involved in this protocol (see Additional file 1).

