### Participants

Eligibility criteria for this trial will be focused on selecting patients with T1D that have a stable insulin regimen and glucose control and are engaged regularly in exercise and physical activities, as this is the target population to whom we would like to generalize the results obtained. Table 1 lists the inclusion and exclusion criteria for this trial. Participants are required to be able to understand instructions for motor and cognitive evaluations and to provide informed consent, in order to be enrolled.

**Table 1 Tab1:** Inclusion and exclusion criteria

Inclusion criteria	Exclusion criteria
Participants older than 18 years More than 2 years of established T1D Stable insulin regimen in the past 6 months indexed by less than 20% change in total insulin daily dose HbA1c less than 9.0% Weekly physical activity of 90 min or more Participation in recreational or competitive soccer-related activities, at least four times per month Participants able to provide informed consent	Any treatment regimen different from continuous subcutaneous insulin infusion or multiple daily insulin injections Any use of medications (other than insulin) known to affect glycemic control including oral or parenteral steroids (except for inhaled steroids), metformin, SGLT2 inhibitors, GLP.1 agonists, thiazolidinedione, sulfonylureas, DPP-4 inhibitors, or any other oral antidiabetic therapy Detectable C-peptide in serum Cognitive impairment comprising any substantial decrease in alertness, language reception, or attention that might interfere with understanding instructions for motor and cognitive testing, not including hypoglycemia unawareness Chronic kidney disease (glomerular filtration rate less than 90 mL · min^-1^) Chronic liver failure (Child-Pugh B or C) Advanced diabetic retinopathy Pregnancy Color blindness

*T1D* type 1 diabetes, *SGLT-2* sodium glucose cotransporter 2, *GLP1* glucagon like peptide 1, *DPP-4* dipeptidyl peptidase 4

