Current ADA guidelines [16] have not yet established any basal insulin dosage adjustment after intermittent exercise, and it remains for the treating physician to decide on a case-by-case basis. However, we have added a modification of 20% of the insulin dose in the interventional arm, based on results obtained from recent trials, an effect seen even with the newer basal insulin such as degludec. [5] Therefore, participants following the sham 4-step method will not receive the post-exercise modification in insulin dosage. However, in order to maintain blinding of the control group, we will provide the unchanged insulin dosage for them to administer in their own homes after the exercise session finishes, in preloaded and concealed insulin syringes, whereby they will not be able to ascertain the dose that has been served. Moreover, and with the aim of increasing adherence, the participants will be contacted through phone calls in order to remind them about eating the before-bedtime snack and to self-administer the insulin treatment provided by the trial.

At 8:00 a.m. on the morning following each training assessment, participants will return to the laboratory. Here we will obtain another fasting blood sample from them via venipuncture and subsequently provide them with a standardized breakfast meal (sugar-coated corn flakes, peaches, semi-skimmed milk). With this meal, they will self-administer their full unchanged rapid-acting insulin dose.

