After completing the first evaluation, participants will change their interventional arm, and both groups will receive a second educational session (visit 5) from an endocrinologist, who will explain the details of their new dietary and pharmacological interventions. Also in this visit, we will assess the efficacy of blinding by asking participants in which interventional arm they think they are allocated, and how confident they are about their answer.

Furthermore, participants will be seen the day following each assessment visit (visits 4 and 7) during which cognitive testing and self-monitoring of blood glucose will be repeated. In the last visit (visit 7) we will assess the efficacy of blinding again by asking participants in which interventional arm they think they were allocated, and how confident they are about their answer.

All participants will be instructed to replicate and record their diets (MyFitnessPal App®) and maintain their current insulin regimen, without modifying the dose, injection site, or time of injection for 24 h before each experimental trial day (visits 3 and 6). Participants will also be instructed to maintain similar grades of physical activity during the trial, avoiding strenuous exercise during the previous 48 h and 48 h following the simulated soccer drills.

The assessment sessions will occur on two separate days (separated by 3 weeks) and consist of both cognitive and physical activity evaluations. During the physical activity assessments participants’ heart rate (HR) will be traced with a Garmin Vivofit 2 Bundle with HR monitor (Garmin^©^, Kansas, USA).

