#### Loughborough Soccer Shooting Test (LSST)

The LSST is also a validated test [21] that allows us to evaluate the capacity of a player (in this case our subjects) to score a goal within a simulated soccer gameplay scenario. This particular aspect of the test reproduces real-life conditions of gameplay, thus yielding a more real score of the subject’s performance.

Immediately following completion of the LSPT protocol, the participants will be evaluated with another capillary finger glucose level. After that, the trainer will proceed with the evaluation of the LSST (see Fig. 3).

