### Adverse event monitoring

An un-blinded group of physicians and physical trainers will be in charge of monitoring glucose derangements and physical injuries that may arise during the assessments. We have prepared protocol-based treatment and dietary interventions that follow guidelines established for both the usual recommendations and the 4-step method groups, which will be executed in the case of hyperglycemic or hypoglycemic events. Also, we will record any adverse events observed during the execution of the trial and, if required, report them directly to our Ethics Committee for further evaluation. Additionally, our technical team will check and calibrate each of the glucometers and CGM devices before using them in any of the protocol assessments.

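### The protocol claims subject and evaluator blinding, but the procedures it describes mask participants at most to which regimen is experimental, and its text on the blinding check and the scorers needs reconciling.

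*Protocol article*

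**What the plan says.** - **Claim.** Trial design: "This is a randomized, crossover, double-blinded (subject and evaluator), controlled trial". The Blinding section repeats it for participants and assessors. It explains that a sham scheme is meant to make both periods feel experimental, although the insulin and diet differ.
- **Rapid-acting insulin.** Active intervention: before the session "they will self-administer a 50% reduced pre-meal rapid-acting insulin dose into the abdomen", and a second halved dose is self-injected with the post-exercise meal. No concealment is described for rapid-acting doses in either period.
- **Basal insulin.** In the real period it is cut by 20%, with no masking described. In the control period it is unchanged and is supplied "in preloaded and concealed insulin syringes, whereby they will not be able to ascertain the dose that has been served"; the stated purpose is to keep the control group blinded.
- **Teaching.** An un-blinded endocrinologist gives the insulin and diet instructions at visit 2. At visit 5 participants meet an endocrinologist "who will explain the details of their new dietary and pharmacological interventions".
- **Eligibility.** Table 1 excludes "Any treatment regimen different from continuous subcutaneous insulin infusion or multiple daily insulin injections", so pump users can enter.
- **Blinding check.** Outcomes, on visit 5: "Also in this visit, we will assess the efficacy of blinding by asking participants in which interventional arm they think they are allocated". It is repeated at visit 7. The Blinding section says the check comes before the switch and at the end. Table 3 marks visit 5 and the shared column for visits 4 and 7.
- **Evaluators.** The Blinding section says every soccer and cognitive assessor is blinded and names only physicians as un-blinded. Adverse event monitoring: "An un-blinded group of physicians and physical trainers will be in charge of monitoring glucose derangements". LSST section: "the trainer will proceed with the evaluation of the LSST".

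**The concern.** Subject blinding is offered as a property of the design, and readers will weigh the results accordingly. If participants can tell the regimens apart, a difference in an effort-dependent or self-reported outcome may partly reflect what they expect of each regimen, yet it would be reported as double-blind evidence. In a crossover this matters more than in a parallel trial, because each participant meets both regimens and can compare them directly.

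The planned questionnaire is the only check on whether the masking worked. If its timing makes the answers hard to interpret, the trial cannot show afterwards that the label was earned.

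**Working it through.** No arithmetic applies: the protocol gives no figure for blinding. The check sets its statements side by side.

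**1. Can a participant distinguish the two periods?**

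| Element | Real 4-step period | Control period | Masking described |
|---|---|---|---|
| Rapid-acting dose before exercise | Halved, self-injected | Reduced by a different amount | None |
| Rapid-acting dose after exercise | Halved, self-injected | Usual dose | None |
| Drink with post-exercise meal | Isomaltulose orange drink | Water | None |
| Bedtime snack | Yogurt with honey | Orange juice and half a banana | None |
| Basal dose | Cut by 20% | Unchanged | Concealed syringe, control period only |
| Teaching beforehand | Regimen explained | Regimen explained | Not applicable |

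(For the control dose before exercise, the text gives 75% of the usual dose and Table 2 a 75% reduction. The two must be reconciled, but on either reading the dose is reduced and differs from the real period.)

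Participants have had type 1 diabetes for more than two years and have been on a stable regimen for six months, so they know their usual doses. The post-exercise dose, the drink, the snack and the teaching each separate the periods without help from the others. As described, the regimens are distinguishable.

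**2. What does the concealed syringe achieve?** It hides one dose in one period. If the real period has no matching syringe, the device itself differs between periods. It cannot conceal a basal rate set on a pump.

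**3. What masking is left?** The Blinding section's own aim: participants are not told which regimen is the experimental one. Table 3 names the two regimens in its row for the educational sessions, but the protocol does not say whether participants hear those names. This narrower masking is therefore the most that can be claimed.

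**4. When is the blinding question asked?** Outcomes first says that participants change arm after the first evaluation. It then describes visit 5, with the new teaching and the question in the present tense. An answer could refer to the period just finished or to the one about to start. The Blinding section places the question before the switch. The two accounts do not agree, and the order of teaching and question within visit 5 is not given.

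**5. Who scores?** Three statements meet: all soccer assessors are blinded; physical trainers belong to the un-blinded group; a trainer evaluates the LSST. All three can be true only if that trainer is not one of the un-blinded trainers, and the text does not say so. The LSPT is scored by evaluators whom nothing links to the un-blinded group.

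**6. Which outcomes are exposed?** Most exposed are effort in the self-paced part of the LIST-P, soccer and cognitive scores, and the hypoglycemia categories that depend on symptoms. Less exposed is the primary outcome, which needs a confirmed glucose value at or below 60 mg/dL, with scheduled self-measurement, CGM and standardized meals around the session.

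**The case against.** The strongest defence is that the protocol never claims the regimens are indistinguishable. The Blinding section accepts that they differ and aims only to hide which one is the real method. Teaching both regimens fits that aim. So does awareness of a reduced dose, because both periods reduce the dose before exercise and omit insulin with the snack. This stands as an account of what was intended. It is still a narrower property than subject blinding, and the control section goes further by saying that the concealed dose cannot be ascertained.

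Stronger readings are tempting, and the document does not support them:

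- *Participants are shown their doses.* Nothing says so. The percentages are addressed to the reader, and awareness is an inference from self-injection and the teaching.
- *Every injection user will recognise the control period by its syringes.* This rests on silence about the real period. The Randomization section has the pharmacy prepare insulin for whichever arm is assigned, so concealment in both periods may be intended.
- *An un-blinded trainer scores the LSST.* The two trainer roles are not identified with each other, Baseline assessments mentions a separate soccer trainer, and the Blinding section says the opposite.
- *The visit 5 answers are contaminated by the teaching.* That assumes the teaching comes first. The visit 7 question looks back and has no later teaching.

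A full protocol may settle some of this. The point concerns statements that do not fit together here, not omitted detail.

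**Conclusion.** The concern holds in limited form. As described, the procedures do not deliver full subject blinding; what remains is, at most, masking to which regimen is experimental. The timing of the blinding question differs between two sections, and the trainer's status is ambiguous.

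The conclusion rests on the article's text and on experienced patients noticing differences in food and in their own doses. It does not depend on the syringe inference, since the visible foods and the teaching suffice.

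A reader might want to attach a bias to the primary comparison. No size can be derived from the document: any count of participants whose outcome changed would be invented. What can be said is an ordering: effort, skill, cognitive and symptom outcomes are more exposed than glucose-confirmed events. The matter should be corrected because it changes what the trial can claim.

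**What to change.** 1. Describe the trial as assessor-blinded, with participants masked only to which regimen is experimental, and use that wording in Trial design and Blinding.
2. For injection users, supply basal insulin in identical concealed syringes in both periods. State that pump users are not dose-blinded.
3. Ask the blinding question about the period just completed, at visit 4 or before the visit 5 teaching, and again at visit 7. Align Outcomes, Blinding and Table 3.
4. State that the LSST and LSPT scorers are not members of the un-blinded group in Adverse event monitoring, and reconcile the three sections on roles.

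The cost is protocol wording, the same syringe preparation in the second period, and possibly moving one questionnaire. The downside is a weaker blinding label. No dose or clinical rule changes. Trial status gives recruitment as pending, so as the article stands these changes could precede enrolment.
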